#### **Background**

Neck pain is a common and challenging health problem in the world population, with average lifetime prevalence of 48.5% [1]. It is experienced by people of all ages, with the 12-month prevalence of any neck pain among adults ranged from 12.1% to 71.5% and among children ranged from 34.5% to 71.5% [2].

In Hong Kong, neck pain was highly prevalent with increasing impact [3-4]. The 12-month prevalence of neck pain was 64.6% and around 38.0% suffered from moderate to severe pain [4]. Neck pain caused disturbances to social and work functions. There were about 17.7% of these neck pain patients had to limit their social activities and 19.0% had to limit their work [4]. Moreover, approximately 25.0% of neck pain patients have consulted medical or health professionals and it demonstrated a general trend that more neck pain patients used complementary therapies, including acupuncture [3-4].

There are different types of definitions and classification for neck pain in literature based on anatomical location, etiology, severity, and duration of symptoms [5]. According to the Bone and Joint Decade 2000-2010 Task Force on Neck Pain and Its Associated Disorders, neck pain was specific to pain located in the anatomic region of the neck, with or without radiation to the head, trunk and upper limbs [6]. The

anatomic region of the neck from the back referred to the region from the superior nuchal line to the spine of the scapula and the anatomic region of the neck from the side referred to the region from the superior nuchal line down to the superior border of the clavicle and the suprasternal notch.

There are various invasive and noninvasive treatment options available for patients with neck pain, including medications, injection, manual therapies, physical modalities, complementary and alternative medicine therapies, education or advice, and surgery [7-8]. However, due to the paucity of evidence from primary studies, the efficacy of currently available treatments for neck pain remains unclear [9-10].

Abdominal acupuncture is a therapeutic intervention based on traditional Chinese medicine acupuncture meridian theory and new concepts developed by [name] Bo after decades of research [11]. According to abdominal acupuncture, acupuncture needles are used to stimulate the abdominal meridian system. The abdominal meridian system is a network of meridian and acupuncture points governed by the *shenque* system. It is based on the idea that, the acupuncture point Shenque (CV8) formed the foundation of all regulating systems of the body at the embryological stage, regulating the distribution of qi and blood to the whole body [12]. By puncturing specific acupuncture points on the abdomen, the system can be used to restore harmony and achieve a holistic balance of the body. There are three levels of needle penetration in abdominal acupuncture with distinctive functions and therapeutic effects, in which deep needling is used to regulate the viscera and bowels; medium needling is used to regulate the meridians and shallow needling is used to treat symptoms. During abdominal acupuncture treatment, the skin tissue is needled through its superficial layers. With the needles insertion mainly on the superficial skin, abdominal fat down

to the superficial layer of abdominal muscle, abdominal acupuncture is safe and no injury would be found on the abdominal organs. The treatment is rather painless and more acceptable to patients as needle penetration is much shallower than conventional techniques and obtaining qi will not be elicited. Abdominal acupuncture can be used in treatment of various disorders, including in particular pain and neurological disorders. By concentrating acupuncture on specific points and areas on the abdominal region, all parts of the body can be treated as the energy of the whole body is connected [11-14].

Previous reviews and studies on acupuncture treatments have shown positive effect on pain relief for various disorders, including headache, neck and shoulder pain and back pain [15-19]. As regards to neck pain, the results from two systematic reviews on randomized controlled trials showed that abdominal acupuncture had positive effect for treatment of neck pain, including pain relief in terms of improvements on visual analogue scale (VAS) on pain, pain rating index (PRI) and present pain intensity (PPI) by using the McGill pain questionnaire [20-21]. However, due to the lack of large sample size, high quality and well-designed studies, its effectiveness is still inconclusive [16,19-21].

In view of the importance of the health problem of neck pain, a carefully designed randomized, placebo-controlled, patient and assessor-blind clinical trial is proposed.

## **Objectives**

This study aims to evaluate the efficacy of abdominal acupuncture for the treatment of neck pain. It will examine whether abdominal acupuncture treatment can reduce neck pain disability and intensity, and improve quality of life for neck pain patients.

## **Methods**

### ***Study design***

This study is a single center, patient and assessor-blind, placebo-controlled, parallel-group study with balanced randomization that compares standardized abdominal acupuncture with controlled non-penetrating sham abdominal acupuncture. The trial will be conducted at Pok Oi Hospital – The Chinese University of Hong Kong Chinese Medicine Centre for Teaching and Research (Shatin). Clinical ethics approval will be obtained from the Joint CUHK–NTEC Clinical Research Ethics Review Committee before the trial starts. Eligible participants are blinded to treatment group allocation. The participants will be told before randomization that they are allocated to one of two groups. They will be informed that the treatment might or might not prove to be effective and that there will be a 50% chance of assigning to a sham group but do not tell what the sham treatment is. The outcome assessment and statistical analysis will be performed by a research assistant who is also blinded to patient assignment.

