### ***Recruitment***

Participants will be recruited through advertisements or posters posted on bulletin boards of all Chinese medicine centers, polyclinics and mobile clinics under Pok Oi Hospital and leaflets delivered through these sites. Patients interested in participating in the study will be referred to Pok Oi Hospital – The Chinese University of Hong Kong Chinese Medicine Centre for Teaching and Research (Shatin) to undergo a process to determine eligibility. They will be first screened and checked by Hong Kong Registered Chinese Medicine Practitioners (RCMPs) who have at least 3 years clinical experience and have received pre-study training by a senior RCMP. The RCMPs will run down the checklist of inclusion and exclusion criteria. A full medical history will be obtained, as well as clinical examination and cervical radiography. The clinical examination consist of inspection of the neck and shoulder regions for muscle

atrophy and dislocations, active and passive movements of neck and shoulder joints and provocation tests of neck and shoulder muscles. Those suitable to be recruited to the study will be asked to see the research assistant of the center. Then, the research assistant will explain the overall objectives and nature of the study and guides them through the informed consent process. The research assistant will administer the baseline questionnaire and written informed consent. This is followed by random allocation to real abdominal acupuncture group or sham abdominal acupuncture group by an administration staff of the Chinese medicine center. After randomization, the research assistant will schedule treatment procedure. The study flow is shown in Figure 1.

Figure 1. The study flow of abdominal acupuncture for neck pain

[figure not shown]

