### *Sham abdominal acupuncture treatment*

In the sham treatment group, single-use, disposable non-penetrating blunt sham needles with guide tubes will be used. The acupuncture points used will be 1 *cun* away from the points used in the real abdominal acupuncture group. After the skin sterilization, the RCMP will mimicked the real abdominal acupuncture treatment by using the blunt sham needle with the patient lying in a supine position and wearing eye mask. The RCMP will pretend to insert needle using guide tubes similar to real abdominal acupuncture treatment. When the needle is pressed on the skin, the blunted tip will touch the skin, giving patient feeling of real needle insertion. The treatment procedure and techniques used in this group will be the same as the real treatment group. An infrared therapeutic lamp (Chongqing Xinfeng Medical Instruments Co., Ltd, China) will be placed 30 cm directly over the navel for the duration of the

30-minute retention time in each treatment session.

After the completion of the 4-week follow-up, the patients randomized to this group will receive compensation treatments of real abdominal acupuncture as described in the real treatment group.

Throughout all the treatment sessions for both real and sham abdominal acupuncture groups, a screen and eye masks will be used to obstruct patients' sight from seeing the needles.

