### *Primary outcome measure*

The primary outcome measure is the Northwick Park Neck Pain Questionnaire (NPQ) [29]. It is a questionnaire used to evaluate functional performance in patients with neck pain [5]. In this study, the validated Chinese version of the NPQ will be used [30-32]. It consists of nine five-part questions to assess the patient's symptoms and a score is obtained [29]. The questions cover activities which are likely to be affected

by neck pain. Each question contains five statements of increasing difficulty and is scored between 0 to 4. The NPQ will be scored out of 36, or 32 for non-car drivers, and is presented as a percentage [29,33]. In this study, the questionnaire will be assessed at baseline, immediately after the intervention ends, at 4-week, and 12-week follow-up interviews for real abdominal acupuncture group. As for sham abdominal acupuncture group, the questionnaire will be assessed at baseline, immediately after the intervention ends, and at 4-week follow-up interview.

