### *Secondary outcome measures*

The visual analogue scale (VAS) for pain is a measurement of pain intensity and has widely used [5,34]. This is a continuous scale of 10-cm in length. Participants will be asked to mark on the scale 0 (no pain) to 10 (worst imaginable pain), the degree of intensity of neck pain experienced on the day the assessment is performed. This item will be assessed at baseline, after the first treatment, immediately after the intervention ends, at 4-week, and 12-week follow-up interviews for real abdominal acupuncture group. As for sham abdominal acupuncture group, it will be assessed at baseline, after the first treatment, immediately after the intervention ends, and at 4-week follow-up interview.

The SF-36 Health Survey is a generic questionnaire that used to measure the general health status, including physical and mental components, with higher scores indicate better health [5,35]. In this study, the validated Chinese (HK) SF-36v2 Health Survey will be used [36]. This measure will be assessed at baseline, immediately after the intervention ends, at 4-week, and 12-week follow-up interviews for real abdominal acupuncture group. As for sham abdominal acupuncture group, it will be assessed at baseline, immediately after the intervention ends, and at 4-week follow-up interview.

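### The declared blinding of the analyst, and of the assessor at week 12, cannot hold as written because after week 4 the two arms follow different schedules

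*Protocol*

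**What the plan says.** Protocol, Study design, makes an explicit claim about both assessment and analysis: "The outcome assessment and statistical analysis will be performed by a research assistant who is also blinded to patient assignment".

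The outcome sections then set different schedules for the two arms:

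- **NPQ (Primary outcome measure).** The real arm is assessed at baseline, at the end of treatment, and "at 4-week, and 12-week follow-up interviews for real abdominal acupuncture group". For the other arm: "As for sham abdominal acupuncture group, the questionnaire will be assessed at baseline, immediately after the intervention ends, and at 4-week follow-up interview".
- **VAS (Secondary outcome measures).** The real arm again has a week-12 assessment. For sham, "it will be assessed at baseline, after the first treatment, immediately after the intervention ends, and at 4-week follow-up interview".
- **SF-36v2 (Secondary outcome measures).** The real arm has week 12. "As for sham abdominal acupuncture group, it will be assessed at baseline, immediately after the intervention ends, and at 4-week follow-up interview".
- **Table 1** shows the same split, with separate Real and Sham rows for these three instruments and a week-12 mark in the Real rows only.

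Sham abdominal acupuncture treatment adds a second difference: "After the completion of the 4-week follow-up, the patients randomized to this group will receive compensation treatments". No such sessions are planned for the real arm.

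Two further statements limit the consequences. The section on baseline information places the primary endpoint at the end of the intervention. Statistical methods and analysis restricts the repeated-measures comparison of the arms to baseline, end of treatment and week 4.

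**The concern.** Blinding the analyst guards against choices in data cleaning or analysis that are influenced by knowing which arm is which. The guard matters here because the statistical section names a repeated-measures ANOVA, ANOVA at separate assessments and independent t-tests for the same outcomes. If the file itself shows which arm is which, the trial report would claim a safeguard that the design removes.

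The same schedule affects the week-12 interviews. NPQ, VAS and SF-36v2 are patient-reported, but they are collected at interview by an assessor said to be masked. At week 12, being due these instruments is itself evidence of the arm. Those data also have no concurrent control, so a change from baseline in the real arm cannot be separated from natural recovery or from regression to the mean after entry on a minimum pain score.

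**Working it through.** The protocol gives no figure for this point, so the check sets the schedules and roles side by side.

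**Step 1. Planned assessments by arm** (outcome sections and Table 1; 77 patients per arm from Sample size determination):

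| Time | Real arm: NPQ, VAS, SF-36v2 | Sham arm: NPQ, VAS, SF-36v2 | Do the schedules differ? |
|---|---|---|---|
| Baseline | 77 | 77 | No |
| End of treatment (primary) | 77 | 77 | No |
| Week 4 | 77 | 77 | No |
| After week 4 | no compensation sessions | compensation sessions | Yes |
| Week 12 | 77 | 0 | Yes |

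The VAS taken after the first treatment is the same in both arms. During treatment both arms attend six sessions over two weeks, so the visit pattern reveals nothing up to and including week 4.

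**Step 2. What the assessor learns.** Anyone conducting a week-12 NPQ, VAS or SF-36v2 interview under this plan is interviewing a real-arm patient. The share of planned week-12 questionnaires that belong to the real arm is 77 / (77 + 0) = 100%.

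**Step 3. What the analyst learns.** Suppose the file carries a group code A/B and the week-12 fields. The code with week-12 values is the real arm. Dropout does not hide this. If the planned 15% were all lost before week 12, about 77 × 0.85 = 65 real-arm patients would still have values, against 0 in the sham arm. Once the code is read, it also labels patients who left before week 4, because they carry the same code.

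**Step 4. What is needed to read the code.** Without a group code, a patient lost by week 4 cannot be placed from the visit pattern alone. Table 1 also lists medication use, adverse experiences and dropouts at week 12 without splitting them by arm, so a week-12 contact by itself is not proof of real treatment. The week-12 questionnaire values are.

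**Step 5. What stays intact.** For each patient, the end-of-treatment and week-4 outcomes are recorded before the row at which the schedules part. This mechanism does not reach their collection.

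**The case against.** The strongest reply is that the controlled comparison is largely protected already. The primary endpoint comes before the split, the between-group ANOVA stops at week 4, and the protocol states no week-12 hypothesis or durability claim. Missing-data handling is fixed as last value carried forward, so it is not open to the analyst's discretion. Data locks and coded files are also commonly left to a statistical analysis plan, which may exist. Most of this stands, and it confines the point to the blinding of the analysis and of the week-12 assessment. It does not remove the point: the protocol itself declares a blinded analyst and itself sets the schedule that undoes the blinding, so this is a contradiction in its text and not a missing detail.

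Three stronger readings are tempting but unsupported:

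- **That one person does everything.** A reader might infer that a single research assistant schedules, interviews and analyses. Recruitment says "After randomization, the research assistant will schedule treatment procedure", but that concerns a course of sessions identical in both arms and reveals nothing. The protocol does not say that the same individual fills each role, nor who arranges the visits after week 4. The point does not need this, since a separate analyst given the week-12 data could read the code equally well.
- **That the primary outcome was collected unblinded.** The schedules part only after week 4.
- **That patients in both arms learn their allocation.** Sham patients may infer it when offered compensation sessions. The protocol does not say that real-arm patients know of the offer. In either case this comes after the compared assessments.

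**Conclusion.** The point holds in a limited form. As written, the statement that the analyst is blinded fails for any file that combines a group code with week-12 outcomes. The statement that the assessor is blinded fails for the week-12 interviews. The size of the problem is complete separation on those fields: 77 planned real-arm patients against none.

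This rests on two conditions: that the schedule is followed as stated, and that the analyst works on a file that includes week 12, which the protocol does not exclude. The conclusion that primary and week-4 collection is unaffected assumes that whoever assesses patients does not also see a decodable group code while others are still under assessment; nothing in the protocol suggests otherwise.

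No bias in the primary result is shown. A safeguard that the protocol claims is lost, and it can be restored at almost no cost. The week-12 data lack a control, but they already sit outside the between-group ANOVA, so the remaining need there is a plain statement of their status.

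**What to change.** 1. State that the dataset covering baseline, end of treatment and week 4 will be locked, and that the real-versus-sham analysis will be run on it under coded arm labels before any week-12 or compensation data are added or shown to the analyst.
2. State that the week-12 results come from the real arm only, are unblinded and uncontrolled, and will be reported descriptively, with no claim of efficacy or durability.
3. If the first step is not adopted, withdraw the statement that the analyst is blinded. In either case, limit the claim of assessor blinding to assessments up to and including week 4.

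The cost is a two-stage data file and slightly more administration. No treatment, visit or sample size changes.

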### ***Participants***

This study will focus on patients aged between 18 and 65 years with neck pain. Entry inclusion and exclusion criteria are developed mainly to enroll appropriate participants and exclude those with complicated neck pain or having serious diseases.

### ***Inclusion criteria***

Patients will be included in the study if they satisfied the following criteria:

- between 18 and 65 years of age with the ability to speak and understand Cantonese;

- neck complaints on:
  - pain, stiffness or tenderness, with or without musculoskeletal signs including decreased range of motion and point tenderness [22];
  - pain felt in the neck with radiation to the occiput or towards the shoulders, or both with limitation of neck motion [22];
  - neck pain with degenerative joint disease or cervical spondylosis, or both [22];
- 3 points or more on a 10-cm visual analogue scale for neck pain at the time of screening;
- no previous treatment with abdominal acupuncture for any reason;
- agreed to be randomized; and
- agreed to sign the informed consent form.

### *Exclusion criteria*

Patients will be excluded from the study if they possess any of the following criteria:

- visceral pain in the neck, including carcinoma of thyroid or larynx and tuberculosis of larynx [22];
- serious spinal disorders, including malignancy, vertebral fracture, spinal infection and inflammatory spondylitis;
- patients who previously had neck surgery or are scheduled to have one during the study;
- other chronic diseases that could interfere with abdominal acupuncture treatment effects, including cardiovascular disease, diabetic neuropathy, active hepatitis, fibromyalgia, rheumatoid arthritis, dementia and epilepsy;
- diagnosis of cancer of any nature;
- chief musculoskeletal pain other than neck pain;

- conditions that abdominal acupuncture might not be safe, including clotting disorders, administration of an anticoagulant agent, acute abdominal disorders, venous dilation of the naval, celiac tumor and pregnant women;
- possess abdominal scar which will affect the proper selection of acupuncture points for abdominal acupuncture;
- severe psychiatric or psychological disorder;
- acupuncture treatment for neck pain during the previous month;
- conflicting or ongoing co-interventions (drugs or alternative treatments, or both);
- engage in any other clinical trial during the study period;
- pending neck-related litigation or disability claims;
- incapacity to complete the questionnaires or to answer the questions of the assessor in the study; and
- pregnant and breast feeding women.

### ***Recruitment***

Participants will be recruited through advertisements or posters posted on bulletin boards of all Chinese medicine centers, polyclinics and mobile clinics under Pok Oi Hospital and leaflets delivered through these sites. Patients interested in participating in the study will be referred to Pok Oi Hospital – The Chinese University of Hong Kong Chinese Medicine Centre for Teaching and Research (Shatin) to undergo a process to determine eligibility. They will be first screened and checked by Hong Kong Registered Chinese Medicine Practitioners (RCMPs) who have at least 3 years clinical experience and have received pre-study training by a senior RCMP. The RCMPs will run down the checklist of inclusion and exclusion criteria. A full medical history will be obtained, as well as clinical examination and cervical radiography. The clinical examination consist of inspection of the neck and shoulder regions for muscle

atrophy and dislocations, active and passive movements of neck and shoulder joints and provocation tests of neck and shoulder muscles. Those suitable to be recruited to the study will be asked to see the research assistant of the center. Then, the research assistant will explain the overall objectives and nature of the study and guides them through the informed consent process. The research assistant will administer the baseline questionnaire and written informed consent. This is followed by random allocation to real abdominal acupuncture group or sham abdominal acupuncture group by an administration staff of the Chinese medicine center. After randomization, the research assistant will schedule treatment procedure. The study flow is shown in Figure 1.

Figure 1. The study flow of abdominal acupuncture for neck pain

[figure not shown]

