### ***Ethical considerations***

This study will adhere to the common guidelines of the Declaration of Helsinki for medical research involving human subjects [26-27] and the International Conference on Harmonisation – Good Clinical Practice Guidelines [28]. Prior ethical approval will be obtained from the Joint CUHK–NTEC Clinical Research Ethics Review

Committee before the commencement of the study. Prior verbal and written consent will be obtained from each patient participating in the study.

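### The Recruitment section places eligibility procedures, cervical radiography included, before the formal explanation of the study and written consent, and describes no consent step for candidates found unsuitable

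*Protocol*

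**What the plan says.** The protocol's Recruitment section sets out an order. Advertisements, posters and leaflets bring in candidates: "Patients interested in participating in the study will be referred to" the trial centre to have their eligibility determined. Registered Chinese medicine practitioners see them first and work through the inclusion and exclusion checklist. Within that step, "A full medical history will be obtained, as well as clinical examination and cervical radiography". The section continues: "Those suitable to be recruited to the study will be asked to see the research assistant of the center". Next comes the explanation: "Then, the research assistant will explain the overall objectives and nature of the study and guides them through the informed consent process". The following sentence reads "The research assistant will administer the baseline questionnaire and written informed consent". Random allocation comes after that.

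Two other sections bear on this:

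- **Ethical considerations:** "Prior verbal and written consent will be obtained from each patient participating in the study".
- **Inclusion criteria:** the last two items are that the patient has agreed to randomization and has agreed to sign the consent form.

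**The concern.** Cervical radiography exposes the candidate to radiation. The Recruitment section places it inside the process for deciding eligibility and does not describe it as usual care. A site following the section literally would carry it out before the candidate has had the formal explanation or signed anything. A candidate who is then found unsuitable leaves without any described consent. A candidate who is found suitable, hears the explanation and declines has been through radiography for a trial that he or she would not have joined. According to the Study design section, what is disclosed before randomization includes a 50% chance of sham treatment, and that could well lead some to decline.

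The point does not touch the estimate, the analysis, blinding or power. It concerns the protection of candidates and whether the protocol can be carried out consistently as written.

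**Working it through.** No arithmetic applies. The check is to lay out the sequence in Recruitment and compare it with the other two sections.

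**Order in Recruitment**

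1. Candidates who have shown interest are referred to the centre.
2. Practitioners screen them: checklist, history, examination, cervical radiography.
3. Those found suitable are sent to the research assistant.
4. The research assistant explains the study and leads the consent process. The sentence opens with a word of sequence, so this step follows step 3.
5. The baseline questionnaire and written consent are administered. One sentence names both, the questionnaire first.
6. Allocation follows.

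Radiography is in step 2 and consent is in steps 4 and 5. No earlier consent, verbal or written, is described. Passage from step 2 to step 3 depends on being found suitable, so screen failures never reach steps 4 and 5.

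**Against Ethical considerations.** The commitment to prior consent has two possible readings:

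- Prior to enrolment and randomization: the Recruitment order satisfies it, because steps 4 and 5 come before step 6.
- Prior to any study procedure: the Recruitment order does not satisfy it, because step 2 comes before steps 4 and 5.

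The section does not say which is meant. It also covers only patients who take part, so it gives no assurance about those screened out.

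**Against Inclusion criteria.** The checklist belongs to step 2. Two of its items concern agreement to randomization and to signing the consent form. A candidate cannot meaningfully agree to either before the explanation in step 4. So either the checklist cannot be completed where Recruitment puts it, or some explanation is given earlier than Recruitment says. This mismatch exists whichever reading of prior consent is adopted.

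**Who is affected.** Sample size determination plans 154 randomized patients (77 per group). All of them would pass through step 2 before consent and would consent before allocation. The protocol gives no number of candidates to be screened, so the number of screen failures cannot be stated.

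**The case against.** Four stronger readings are tempting, and the protocol does not support them.

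- **A reader might infer that candidates know nothing of the study when they are screened.** They respond to study advertising and are described as interested in taking part, and a practitioner could hardly complete the checklist without mentioning randomization and consent. Only the formal explanation is placed later.
- **A reader might infer that Recruitment contradicts Ethical considerations.** That would require prior consent to mean consent before screening. The text does not say so and limits the promise to participating patients. The sections are unreconciled, which is less than contradictory.
- **A reader might infer that candidates undergo research imaging without agreeing to it.** The protocol does not say whether recent clinical films would be accepted or what agreement is sought for the imaging itself. What can be said is that no consent step is described before it.
- **A reader might infer that data on screen failures could not be reported.** No section sets such a rule or plans such an analysis.

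It is also fair to say that Figure 1, the study flow, could not be seen in the text reviewed and may show a different order. And all randomized patients do consent in writing before allocation.

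These objections narrow the point without removing it. Interest in an advertisement is not the consent process that the protocol itself describes, and the protocol does not say that the advertising discloses the radiography. The order in Recruitment is stated, so this is not a detail left to another document.

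**Conclusion.** The point holds in limited form. Recruitment, read in its natural order, puts study eligibility procedures, radiography included, ahead of the formal explanation and written consent. That order is not reconciled with the undefined promise in Ethical considerations or with the two agreement items in Inclusion criteria.

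For the 154 patients planned for randomization, the defect is one of timing. For screen failures, in unknown number, it is the absence of any described consent step.

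The conclusion assumes that the Recruitment text is meant chronologically, which its wording indicates, and that the radiography is done for eligibility, which is where the section places it. If Figure 1 shows consent first, the text and the figure would still have to be brought into line. The change should be made, but the point does not threaten the validity of the trial's comparison.

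**What to change.** - **Recruitment:** reorder the section so that the research assistant's explanation and the written consent come before any study-specific screening procedure, radiography included, and before the baseline questionnaire. The checklist, history, examination, radiography, questionnaire and allocation then follow.
- **Ethical considerations:** state that consent is obtained before these procedures.
- **Figure 1:** check that it shows the same order, and amend it only if it does not.

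This also resolves the mismatch with Inclusion criteria, since the two agreement items can then be met when the checklist is completed. It spares radiography for those who would decline once the study and the chance of sham treatment are explained.

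The cost is consent time spent on some candidates who prove ineligible. No extra staff or procedures are needed, and the sample size is unchanged.
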